### Sample size calculation

The preliminary analysis of the PREACT study (NCT03013010) showed that preoperative chemotherapy with three cycles of the SOX regimen can yield a pCR rate of 2%, and two cycles of the SOX regimen plus chemoradiation of 45 Gy/S-1 yielded a pCR rate of 17%. The preliminary analysis of a study called NeoPLANET (NCT03631615) showed that the pCR rate of CapeOX plus camrelizumab combined with chemoradiation was 26.7% (4/15). According to poster 4036 of 2021 ASCO, four cycles of mFOLFOX6 plus camrelizumab yielded a pCR rate of 10% (5/52). Thus, with the addition of PD-1 mAb, the increased range of the pCR in both the preoperative ChT group and CRT group was approximately 8 to 10%, which is a reasonable range. Based on these research data, in this study, the pCR rate of Arm A is set as P1 = 26%, and the pCR rate of Arm B is set as P2 = 10%. The null hypothesis (H0): the pCR rate of Arm A is not better than that of Arm B, that is, P1-P2 ≤ 0. The alternative hypothesis (H1): the pCR rate of Arm A can be increased by 16% compared with Arm B, that is, P1-P2 = 16%.

The patients were randomly assigned to two arms at a ratio of 1:1. One side test is adopted, and if the error rate of type I (α) is set to 0.05, then 138 patients need to be enrolled, i.e., 69 in each arm, which can ensure that the test efficiency (1-β) reaches 80%. When the dropout rate is set to 10%, 152 patients are needed, with 76 in each group.

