### Statistics

The EFS will be calculated from the date of randomization to the date of any event or censoring. The event is defined as below: (1) locoregional recurrence; (2) peritoneal seeding; (3) distant metastasis; (4) death of any reason; (5) tumor progression according to RESIST 1.1. The OS will be calculated from the date of randomization to the date of death or the date of the last follow-up. Survival will be estimated by using the Kaplan-Meier method, and differences between the survival curves will be examined with the log-rank test. Fisher’s exact test will be used to compare the patient characteristics between the two arms. Endpoints related to the rate, including the R0 resection rate, pathological response rate, toxicity occurrence, and surgical complications, will be compared between the two arms using the chi-square test. All statistical tests are two-sided. The level of significance is *P* < 0.05.

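### The sample size assumes a one-sided 5% test of pCR, but the Statistics section makes every test two-sided at 0.05. The primary success rule is contradictory, and power is about 70% if the two-sided rule governs.

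*Protocol article*

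**What the plan says.** The primary endpoint is the pCR rate (Primary endpoint section). The Sample size calculation section gives the null hypothesis as "the pCR rate of Arm A is not better than that of Arm B, that is, P1-P2 ≤ 0", so it is directional. The alternative is a 16-point advantage for Arm A, 26% against 10%. On the test itself it says "One side test is adopted, and if the error rate of type I (α) is set to 0.05", and it derives 138 patients, 69 per arm, for 80% power. A 10% dropout allowance raises this to 152, or 76 per arm.

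The Statistics section assigns the chi-square test to endpoints expressed as rates and closes with "All statistical tests are two-sided" and a significance level of P < 0.05. It does not exempt pCR, and nothing elsewhere in the article reconciles the two sections.

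**The concern.** The two sections set different critical values for the same comparison: z = 1.645 for one-sided 0.05 and z = 1.960 for two-sided 0.05. A result favouring Arm A with a one-sided p between 0.025 and 0.05 (two-sided p between 0.05 and 0.10) meets the success criterion of the Sample size calculation section and fails that of the Statistics section.

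Two things are at stake. First, the primary conclusion can turn on which sentence the analyst follows, and the article leaves room for that choice to be made after the data are seen. A reader relying on the Statistics section would take the false-positive risk in favour of Arm A to be 2.5%, when it would be 5% under the other rule. Second, if the two-sided rule governs, the trial is smaller than its stated power requires.

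**Working it through.** **Inputs**, all from the Sample size calculation section: P1 = 0.26, P2 = 0.10, difference 0.16, 1:1 allocation, α = 0.05, power 80%, 69 per arm evaluable, 76 per arm enrolled. The two-sided rule comes from the Statistics section. The normal quantile for 80% power is 0.842.

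**Step 1: reproduce the plan's figure.** With unpooled variance, n per arm = (z_α + z_β)² × [P1(1−P1) + P2(1−P2)] / (P1−P2)². The variance sum is 0.26 × 0.74 + 0.10 × 0.90 = 0.2824.

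- One-sided: (1.645 + 0.842)² × 0.2824 / 0.0256 = 68.2, so 69. This matches the plan.
- Two-sided: (1.960 + 0.842)² × 0.2824 / 0.0256 = 86.6, so 87.

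With pooled variance under the null (mean rate 0.18), the formula gives 71 one-sided and 90 two-sided. The plan's 69 is therefore a one-sided calculation. The enrolment figure also follows: 138 × 1.10 = 151.8, so 152.

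**Step 2: power under each rule.** The unpooled approximation is Φ(0.16 / √(0.2824/n) − z_α). At n = 69 the first term is 2.501, so power is Φ(0.856) = 80.4% one-sided and Φ(0.541) = 70.6% two-sided. The last column below sums the binomial probabilities of all outcomes in which the uncorrected Pearson chi-square test favours Arm A significantly.

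| Per arm | Rule | Unpooled | Pooled | Exact, Pearson chi-square |
|---|---|---|---|---|
| 69 | one-sided 0.05 | 80.4% | 79.4% | 81.0% |
| 69 | two-sided 0.05 | 70.6% | 69.0% | 70.3% |
| 76 | one-sided 0.05 | 83.6% | 82.7% | 84.0% |
| 76 | two-sided 0.05 | 74.7% | 73.3% | 75.0% |

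**Step 3: how often the rules disagree.** At 69 per arm and the assumed rates, the probability of a result that passes one rule and fails the other is 81.0% − 70.3% = 10.7%, roughly one trial in nine.

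**Step 4: an example** with 7/69 pCR (10.1%) in Arm B, using the uncorrected Pearson test:

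| Arm A | One-sided p | Two-sided p | One-sided rule | Two-sided rule |
|---|---|---|---|---|
| 14/69 | 0.049 | 0.097 | positive | negative |
| 15/69 | 0.031 | 0.063 | positive | negative |
| 16/69 | 0.020 | 0.040 | positive | positive |

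**Step 5: what 80% power would need two-sided.** 87 to 90 evaluable per arm, 174 to 180 in total. Dividing the per-arm number by 0.9 for dropout gives 97 to 100 per arm, or 194 to 200 enrolled, against the planned 152.

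**The case against.** The best defence is that the specific statement governs the general one. The Sample size calculation section is the only place that sets the primary hypothesis, its direction and its α, and the Methods paragraph of the abstract also frames the aim directionally, as a higher pCR rate in Arm A. The Statistics section never names pCR. Everything it does name is secondary or descriptive: EFS, OS, patient characteristics, R0 resection, pathological response, toxicity and complications. On that reading the design is correctly sized and the two-sided sentence covers only the other analyses. This may well be what the authors meant, but it is not what they wrote. The list of rate endpoints is introduced as a non-exhaustive one, pCR is a rate, no other test is assigned to it, and the closing sentence covers all tests without qualification.

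Three narrower points stand:

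- The power loss is conditional. It arises only if the Statistics section governs pCR.
- The 70% applies to 69 evaluable per arm. If nobody drops out, the two-sided figure is 73 to 75%, so the shortfall against 80% is about 5 to 10 points.
- The cut-offs in the example assume no continuity correction, which the article does not specify. With a correction, exact power at 69 per arm would be 73% one-sided and 61% two-sided, and 16/69 against 7/69 would no longer be significant two-sided (p = 0.068). The gap between the rules remains.

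A full protocol or analysis plan may already name the primary test. That would resolve the matter in practice, but the article states both rules affirmatively, so for pCR one of them is wrong. One-sided testing at 0.05 in a randomized phase II trial is not itself being challenged.

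**Conclusion.** The concern holds. The article gives two incompatible decision rules for its primary endpoint. The sample size matches the one-sided rule only. Under the two-sided rule, power at 26% versus 10% is 69 to 71% with 69 evaluable per arm, and 73 to 75% if all 76 are evaluable, not 80%. These figures rest on the plan's own rates and a chi-square or normal test without continuity correction. Because the contradiction concerns what counts as success on the primary endpoint, it should be corrected before the primary analysis.

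**What to change.** State in the Statistics section which rule governs pCR, and make the Sample size calculation section agree with it.

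- **If one-sided:** say that the primary pCR comparison is tested one-sided at α = 0.05, as in the sample size calculation, and reported with the matching two-sided 90% confidence interval for the difference. Limit the two-sided 0.05 rule to all other tests. This costs one sentence, and the sample size and stated power are unchanged.
- **If two-sided, same size:** drop the one-sided wording and restate the power as about 70% at 69 evaluable per arm. This needs no extra patients, but the stated power is less favourable.
- **If two-sided with 80% power:** re-size to 174 to 180 evaluable patients, about 194 to 200 enrolled, which is 42 to 48 more than planned.

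The first option is the cheapest and fits the design as sized. Whichever is chosen, record it with a date before the primary analysis, and say whether the chi-square test for pCR uses a continuity correction.

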## Discussion

Before immunotherapy was widely used, perioperative ChT and preoperative CRT have been the standard treatments for LAGC. If stratified by tumor location, the evidence for the use of preoperative CRT is mainly for GEJ tumors, and the evidence for the use of preoperative CRT for middle or distal GC is relatively lacking. Compared with perioperative ChT, perioperative ChT plus preoperative CRT can improve the tumor withdrawal and decline, but whether this benefit can be transformed into a long-term survival benefit is still uncertain. Studies aiming to answer this question from both East and West are ongoing. With the establishment of immunotherapy in the first-line treatment of AGC, an increasing number of studies, including phase III trials, have explored the value of immunotherapy in the perioperative setting. The regimens include different combinations of ChT, RT, targeted therapy and immunotherapy. Therefore, at present, comparing the advantages and disadvantages of preoperative ChT and preoperative CRT seems to be outdated. Based on this background, we designed the NeoRacing study to evaluate the safety and efficacy of perioperative ChT plus PD-1 mAb with or without preoperative CRT, aiming to address which one is the superior treatment in patients with LAGC.

In the PREACT study, our center has accumulated some experience in the preoperative treatment of LAGC. Either three cycles of the SOX regimen or two cycles of the SOX regimen combined with CRT can be well tolerated by patients. The PREACT study requires that each enrolled patient undergo abdominal exploration with peritoneal cytological examination to obtain an accurate preoperative staging. Data have proved that this design is very necessary. The preliminary analysis showed that approximately one-third of the potentially eligible patients were P1 or CY1. Thus, this design is reserved in the NeoRacing study. However, unlike the PREACT study, P0CY1 patients were eligible for the NeoRacing study.

As mentioned before, a series of perioperative immunotherapy studies are underway, mainly single-arm studies in phase I-II, including single ICI, dual ICIs, ChT plus ICI, ChT plus RT plus ICI, or ChT plus antiangiogenic agents plus ICI. The endpoint of most studies is the pCR rate. According to the preliminary results of some studies, the pCR rate of a single ICI is only 3.2% [33]. Compared with ChT alone, ChT combined with ICI can improve the pCR rate. In poster 4036 from the 2021 ASCO (NCT03939962), mFOLFOX6 combined with camrelizumab yielded a pCR rate of 10% [33]. In poster 216 from the 2021 ASCO-GI (NCT04341857), FLOT combined with sintilimab yielded a pCR rate of 18.8% [34]. The combination of ChT, RT and ICI can obtain an even higher pCR rate. In the NeoPlanet study (NCT03631615), a combination of CapeOX and CRT was used for proximal GC and yielded a pCR rate of 26.7%, which has been updated to 33.3% in the 2021 ESMO. Another study named SHARED obtained a pCR rate of up to 42.1% [35]. However, the sample size of these studies is small, so more clinical data are needed.

Several explorative endpoints are being determined in the NeoRacing study to find predictive biomarkers of immunotherapy. The main obstacle to immunotherapy is that the response rate is not ideal. Therefore, on the one hand, we need to find predictive biomarkers of immunotherapy. PD-L1 CPS, MMR, TMB, and EBER are biomarkers that have been studied in GC, but there are still disputes. In this study, the predictive efficiency of these biomarkers will be further validated. Some studies have also shown that the gut microbiota [36] and HP infection [37] will have an impact on the efficacy of immunotherapy. On the other hand, to overcome the resistance to immunotherapy, including primary and secondary resistance, we hope to evaluate the changes in the tumor microenvironment and systemic immune status before and after preoperative treatment and to find the causes and mechanisms of treatment resistance.

Overall, the available study results suggest that the tumor regression obtained by preoperative immunotherapy alone is not ideal, and using a combination with traditional treatment methods such as ChT and/or RT is the way to obtain a good efficacy. Although the pCR rate has been further improved, we still need to answer the question of whether this benefit can be transformed into a survival benefit. To the best of our knowledge, the NeoRacing study is the first randomized controlled study to compare the safety and efficacy of perioperative ChT combined with immunotherapy with or without preoperative CRT.

## Data Availability

Not applicable in this study protocol. The data (such as efficacy and toxicity) produced during and after the trial are available from the corresponding author upon reasonable request.

## Abbreviations

AGC: Advanced gastric cancer
BSA: Body surface area
ChT: Chemotherapy
CPS: Comprehensive positive score
CRT: Chemoradiation
CTCAE: Common Terminology Criteria for Adverse Event
FUSCC: Fudan University Shanghai Cancer Center
GC: Gastric cancer
GEJ: Gastroesophageal junction
ICI: Immune checkpoint inhibitor
LAGC: Locally advanced gastric cancer
mAb: Monoclonal antibody
MMR: Mismatch repair
ORR: Objective response rate
OS: Overall survival
pCR: Pathological complete regression
PFS: Progression-free survival
pRR: Pathological response rate
RECIST: Response Evaluation Criteria for Solid Tumors
SOX: S-1 and oxaliplatin
TIME: Tumor immune microenvironment
TMB: Tumor mutation burden
TRG: Tumor regression grading
